### Setting

The evaluation will be conducted across two NSW local health districts (LHDs). LHDs in NSW are health administrative regions with distinct budgets and governance under Australia’s universal healthcare framework, making up geographically based districts and three specialised networks. The intervention sites will consist of three declared adult mental health inpatient units, with a combined capacity of 75 beds, including ten designated for high observation. Operating 24 hours a day and situated within public hospitals, these units cater to varying levels of mental health treatment and observational needs. Delivering acute care from these units to people from different catchments and adjacent local government areas are peer workers and traditional staff from different disciplines, including but not limited to nurses and nurse educators. These units vary in local care models, restrictive practice rates, peer work involvement, and restrictive practice review approaches.

The control sites will be three declared adult inpatient units within two public hospitals in one LHD. Their total bed capacity is 84, and they are without high observation areas. Clinical input supported identifying these sites, considering the bed capacity and availability of high observation beds. One control site has no seclusion room, making it impossible to observe seclusion events or measure their duration. However, as detailed in the Analysis Plan section, the number of seclusion rooms and high observation beds will be considered for covariate balancing. Similar to the intervention sites, the three control units operate with varying levels of mental health practices and are multidisciplinary.

### Sample

Outcome change measurement and qualitative research within the evaluation depend on two forms of samples: daily aggregates of observed events and individual and nurse participants. Daily aggregates of restrictive practice and physical injury events will be used to analyse these outcomes. In contrast to a ‘per incident’ level, an aggregated approach helps prevent the false impression of completeness [20]. It enables a more accurate evaluation of potential reporting biases in real-world data. On the other hand, people receiving care and nurse participants will be involved in the qualitative strand and survey-based measures.

### Sample size

The sample size for this evaluation was determined using a combination of power analyses, prior research findings, and feasibility considerations. Both quantitative and qualitative approaches were employed.

For event-based analyses, Monte Carlo simulations using the simr package [59] and RStudio [60], were used to estimate the necessary duration of data collection. A Poisson mixed-effects model was applied to synthetic data replicating the initial implementation outcome parameters. To detect a 12% reduction in seclusion rates with 99.30% power, at least 3.60 months of data collection is required. To identify significant changes in physical restraint incidents, a 12-month period is necessary to achieve 90.60% power. In comparison, 10.8 months are required to detect differences in Code Black/ Assist events with 85.20% power. These calculations include a 20% buffer to account for potential attrition and were conducted with an alpha level of 0.50, aligning effect size assumptions with findings from the NSW Safewards evaluation [61]. The NSW Safewards evaluation was chosen as a reference, due to its high methodological quality and relevance to the same geographic and service context as this evaluation, being the only study identified in an overview of systematic reviews with such characteristics [5].

For survey-based measures, sample size estimations were conducted using G*Power 3 [62]. Based on power calculations, a minimum of 135 individual survey responses is required across intervention sites, incorporating a 30% margin for potential exclusions to achieve 95% power. Similarly, a minimum of 60 nurse surveys is necessary, maintaining the same power assumptions and buffer levels.

For the qualitative component, data will be collected through semi-structured interviews and focus groups. At least 15 individual interviews will be conducted at T2 and T4, with additional interviews, if necessary, until data saturation is reached. Additionally, three to five focus group discussions will be conducted per site, including six nurses involved in intervention implementation since baseline. These sample size decisions are informed by systematic reviews on qualitative research methodologies, indicating that such numbers are typically sufficient to achieve thematic saturation in studies using interviews [63] or focus groups [64].

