### The Safe Steps for De-escalation

In a regional adult mental health inpatient unit in New South Wales (NSW), Australia, a lack of structure to therapeutic responding was evident in the absence of a consistent content and approach to de-escalation training, the varying skill levels of nurses in managing distress and conflict, and the persistently high rates of physical restraint and seclusion [31]. In response, a new model was introduced in the unit in 2019 to monitor restrictive practices and up-skill nurses, and implement the 2017 NSW review recommendations on seclusion, restraint, and observation [32]. The model was implemented alongside strength-based review meetings, where nurses received feedback on how well they practice relational competencies. The reviews conducted between January 2019 and March 2020 were linked to a reduction in the use of seclusion (incidence rate ratios [IRR] = 0.37, 95% CI [0.24, 0.57], p < .001), compared to an equivalent timeframe before their implementation [33]. Measures of experienced support by the people receiving care in the unit also increased by 14% in 2019–2020, exceeding the 80% national benchmark [34].

This model is called the *Safe Steps for De-escalation*—or simply the *Safe Steps.* It is a clinician initiative centred on a four-step, user-friendly framework for therapeutic responding that begins with helping the person receiving care to identify the issue or problem, through to establishing expected behaviours. There is evidence for the structure and progression of therapeutic responses in the Safe Steps [35] that offers nurses a platform to exercise their authentic voice and intuitive competencies in supporting work towards making acute units safe. The Safe Steps targets nurses’ relational competencies to increase focus on the self-management of people receiving care and therapeutic relationships. Its implementation is supported by value-based training and regular data-informed restrictive practice review meetings.

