**Fig 2 pone.0325558.g002:**
[figure not shown]
Outcomes and data gathering timeline. CEO-MHS = Consumer Evaluation of Mental Health Services; EI = emotional intelligence; eMeds = electronic medication management system; IMI = intramuscular injection; ims+ = incident management system; ProQOL = Professional Quality of Life; VPC-M-FR = Modified Violence Prevention Climate.

There will be three forms of comparisons within the current evaluation. Between- i) and within-group ii) comparisons will be applied to test the first and second sets of hypotheses. The third will be a between-cluster comparison iii), intended to identify the most active co-occurring therapeutic and nursing responses (clusters) contributing to the Safe Steps’ overall impact. The first set of hypotheses is that implementation units will exhibit greater reductions in the IRR for restrictive practice events, the estimate of restrictive practice duration, and the IRR for physical injuries, compared to control groups and their baseline levels. The second set of hypotheses is that measures of service experience, perceived staff action towards violence prevention, nurses’ professional quality of life, and nurses’ perceived demonstration of emotionally intelligent workplace behaviours at the final time point would be significantly higher than at baseline. The between-group comparisons will be conducted exclusively to address the first objective, as these analyses will depend on accessible routine reports on restrictive practices and physical injuries selected for this purpose. Australian public acute mental health services are legally mandated to report on seclusion and physical restraint events and duration as key performance indicators [52]. Events of physical injuries and sedation via IMI are also routinely documented in established information management systems. These routine measures will help minimise performance and detection bias associated with the lack of blinding. Conversely, conducting a between-group comparison on non-routine measures could be cost-prohibitive and challenging to implement, as exemplified by unmet sample size requirements in previous studies [27]. This evaluation will have no randomisation, although covariate balancing will be applied to between- and within-group comparisons in testing the first set of hypotheses.

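### The stated event-based powers, as described, support only the before-after comparison; the 90.60% for physical restraint cannot be carried over to the comparison with control units

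*Protocol article*

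**What the plan says.** The Sample size section introduces its figures as the sizing for event-based analyses, without limiting them to one comparison. On method it says: "A Poisson mixed-effects model was applied to synthetic data replicating the initial implementation outcome parameters". The results are durations of data collection. For seclusion: "To detect a 12% reduction in seclusion rates with 99.30% power, at least 3.60 months of data collection is required". For physical restraint: "To identify significant changes in physical restraint incidents, a 12-month period is necessary to achieve 90.60% power". For Code Black/Assist it gives 10.8 months and 85.20%. The calculations are said to include a 20% buffer for attrition, to use an alpha of 0.50, and to take effect-size assumptions from the NSW Safewards evaluation. The Analysis plan tests each hypothesis at p < .05.

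The initial implementation is described in the section on the Safe Steps for De-escalation. It took place in a single regional unit, and its seclusion result ("incidence rate ratios [IRR] = 0.37, 95% CI [0.24, 0.57], p < .001") is "compared to an equivalent timeframe before their implementation". No control unit is mentioned.

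The first set of hypotheses (Abstract, end of the Introduction, Design) has two comparators. In the Design section, "implementation units will exhibit greater reductions in the IRR for restrictive practice events", durations and injuries, and this is claimed against control groups as well as the units' own baseline. The Introduction defines the events as seclusion, physical restraint and sedation by intramuscular injection. The Setting section gives three intervention units (75 beds) and three control units (84 beds), and says that one control unit has no seclusion room.

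**The concern.** A larger fall than in the control units is a different quantity from a fall since baseline. It is estimated as one before-after rate ratio divided by another, so the sampling error of the control units is added to that of the intervention units. The description of the simulation fits the simpler quantity: its inputs come from an uncontrolled before-after experience, its targets are worded as a reduction, changes and differences, and no control rate, control unit or interaction term appears.

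The Design and Discussion sections present the control group as a main strength of the evaluation. A reader who applies 90.60% to the controlled comparison of physical restraint could take a non-significant result as good evidence of no effect. The same reader could then rely on the before-after result, which is the one exposed to background trends.

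**Working it through.** **1. Can the stated powers be reproduced?** No. For restraint and Code Black/Assist the article gives no effect size, base rate or variance component. For seclusion, a rough event count follows from the initial result.

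- SE of the log rate ratio = (ln 0.57 − ln 0.24)/(2 × 1.96) = 0.2207.
- With variance 1/E0 + 1/E1 and E1 = 0.37 × E0, E0 is about 76 baseline events in 15 months in one unit.
- Three such units over 3.6 months give about 10% power for a 12% reduction at two-sided 0.05, or 58% at two-sided 0.50. Neither is near 99.30%.

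The next steps therefore take the stated powers at face value and ask only what follows if they are before-after powers.

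**2. Signal-to-noise ratio implied by a stated power.** d = z(1−α/2) + z(power).

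- Restraint, α = 0.05: d = 1.960 + 1.317 = 3.277.
- Restraint, α = 0.50: d = 0.674 + 1.317 = 1.991.
- Seclusion, α = 0.05: d = 1.960 + 2.457 = 4.417.

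**3. Variance of the controlled contrast.** Var(log ratio of rate ratios) = Var(log RR, intervention) + Var(log RR, control). With equal information in the two groups the inflation factor is f = 2. If control information scales with beds, f = 1 + 75/84 = 1.893.

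**4. Power of the controlled contrast.** Power = Φ(d × √(t/f) − z(1−α/2)), with α the level of the final test and t the ratio of 12 months to the months at which the stated power was reached. The effect relative to control is taken to equal the effect that was sized. No effect size has to be assumed for restraint, because it is contained in d.

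Example for restraint, α = 0.05, t = 1, f = 2: 3.277/1.414 = 2.317; 2.317 − 1.960 = 0.357; Φ(0.357) = 63.9%.

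| Physical restraint, 12 months | f = 2 | f = 1.893 |
|---|---|---|
| α 0.05 throughout, 90.60% reached at 12 months | 63.9% | 66.3% |
| α 0.05 throughout, 90.60% reached at 10 months (12 = 10 × 1.2) | 71.8% | 74.2% |
| α 0.50 throughout, 90.60% reached at 12 months | 76.8% | 78.0% |
| Simulated at 0.50, tested at 0.05, 12 months | 29.0% | 30.4% |

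Combining α 0.50 throughout with the 10-month reading gives 80.7% and 81.9%, the highest values found. Every reading is below 90.60%. In the last row most of the loss comes from the change of alpha: the before-after test itself would then have Φ(1.991 − 1.960) = 51.2%.

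**5. Effect of weaker control information.** Weighting losses or variation between units in their change over time would raise f. As an illustration, f = 2.5 with α 0.05 gives 54.5% for restraint at 12 months.

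**6. Seclusion over the full year.** With t = 12/3.6 and f = 2: 4.417 × 1.826/1.414 = 5.703, so power is above 99.9%. With only two control units able to record seclusion, f = 1 + 3/2 = 2.5, and power is 99.9%. Simulated at 0.50 and tested at 0.05, it would be 98.1% (f = 2) or 95.1% (f = 2.5).

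**The case against.** The strongest objection is that the article never says which term was tested in the simulation. Replicating the parameters of the initial implementation describes the inputs, and the effect sizes are said to come from another evaluation whose design is not shown. A condensed article may leave the simulated contrast to the full protocol. This stands in part: that the powers are before-after powers is a strong inference from the text, not something the text states. It does not remove the point, because the article puts the powers forward for all event-based analyses, and everything it says about the simulation fits only one of the two comparisons.

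Other limits also stand.

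- A reader might infer that the controlled part of hypothesis (a) is underpowered throughout. The documents do not support that, since seclusion keeps high power over 12 months by the same scaling.
- A reader might apply the same reduction to the 85.20% for Code Black/Assist. Code Black is not among the events that define hypothesis (a); Table 1 lists it as an additional outcome and the Analysis plan as a confounder for weighting.
- A reader might conclude that restraint has no reserve because it needs the full 12 months. The durations 3.6, 12 and 10.8 are exactly 1.2 times 3, 10 and 9, so the 12 months may already contain the 20% buffer.
- The 12% reduction is stated for seclusion only and should not be read across to restraint.

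**Conclusion.** The point holds in a limited form. As described, the stated powers support the within-group comparison only, and the article shows no power for the comparison with control units. For physical restraint the controlled power is lower than 90.60% under every reading tried. It is about 64-66% at two-sided 0.05, about 72% if the buffer is set aside, 77% if alpha was 0.50 throughout, and 29% if the simulation used 0.50 and the test uses 0.05. A single figure of 64% would claim more than the documents allow.

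These values rest on accepting 90.60% as a before-after power, on control units about as informative as the intervention units, on no variation between units in their change over time, and on no loss of precision from weighting. Relaxing either of the last two would lower them. The direction is secure; the exact size is not.

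**What to change.** In the Sample size section, state that 99.30%, 90.60% and 85.20% refer to the within-group comparison, give the base rates and effect sizes used, and correct or confirm the printed alpha of 0.50 against the p < .05 of the Analysis plan. If the simulation did include control units, say so and name the tested term.

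Then re-run the same simr simulation with the three control units (two for seclusion), with the group-by-period interaction as the tested term, at alpha 0.05. Report that power for the between-group hypothesis, or the smallest detectable ratio of rate ratios over the fixed 12 months of baseline and 12 months of follow-up. Add that a non-significant controlled result is to be read from its confidence interval.

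This needs no further sites, time or data, and changes neither the intervention nor the analysis. The cost is a re-run of existing code and a less favourable stated power.

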### Analysis plan

Quantitative and qualitative analyses will be used to answer the evaluation’s objectives. Consultations with statisticians occurred for the range of statistical treatments employed in this evaluation. Various packages in R [74] and RStudio [60] will be maximised for the quantitative analyses, and Matplotlib [75] will be utilised for visualising outcomes. Each hypothesis will be supported if outcomes are statistically significant at p < .05.

Poisson mixed-effects models [56] will be used for count data and linear regression models for continuous outcomes, to determine whether these outcomes differ according to intervention implementation and time points. Data cleaning and validation, assumption checks, model diagnostics, and follow-up analyses will be undertaken. Negative binomial mixed models, zero-inflated models, and linear mixed-effect models may be used depending on the model’s diagnostics. Covariates in the mixed-effect models will include the acute care unit, calendar month, day, year, and the day within the study period for each daily event aggregate. Model selection will prioritise parsimony and explanatory strength. Inverse probability weighting (IPW) will be applied in the between- and within-group comparisons. Using the ipw package [76], IPW will be used to balance covariates, including but not limited to the average harm scores of daily aggregates, the number of high observation beds, the number of seclusion rooms, and other confounds (i.e., physical restraint and Code Blacks are closely interrelated, influencing each other’s occurrence or implementation [77]). Listed covariates for balancing will be used, subject to the data’s fit and the statistical model’s ability to achieve convergence in the IPW approach.

Hierarchical clustering analysis [78] will support the emergence of co-occurring mental health nursing response clusters, which will then be the fixed effect in modelling differential associations with restrictive practices, physical injuries, and situational aggression. This cluster and regression analysis constitutes the between-cluster comparison to identify the most active response clusters contributing most to Safe Steps’ overall impact.

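### The stated 99.30% power for a 12% fall in seclusion from 3.60 months of data cannot be reconciled with the seclusion rate implied by the article's own initial result

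*Protocol article*

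**What the plan says.** The Sample size section of the protocol article makes this claim for seclusion: "To detect a 12% reduction in seclusion rates with 99.30% power, at least 3.60 months of data collection is required". On method it says: "A Poisson mixed-effects model was applied to synthetic data replicating the initial implementation outcome parameters". It adds that the calculations carry a 20% buffer, that they "were conducted with an alpha level of 0.50", and that effect sizes were aligned with the NSW Safewards evaluation. No baseline seclusion rate, number of units or effect scale is given.

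The section on the Safe Steps for De-escalation gives the one initial seclusion result in the article, from a single regional unit. January 2019 to March 2020, set against an earlier period of the same length, showed a "reduction in the use of seclusion (incidence rate ratios [IRR] = 0.37, 95% CI [0.24, 0.57], p < .001".

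The Analysis plan sets the test level: "Each hypothesis will be supported if outcomes are statistically significant at p < .05". Under Design and under Recruitment and consent, the event data cover a baseline year and one year of follow-up. Under Setting there are three intervention units (75 beds) and three control units, one of which has no seclusion room.

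**The concern.** A 12% relative reduction is a small effect for a count outcome, and detecting it with near certainty takes thousands of events. A few months of seclusions in three inpatient units would not normally supply them. The initial result allows a check, because its confidence interval shows roughly how many events one unit produced in 15 months.

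Seclusion is one of the hypothesised effectiveness outcomes, and 99.30% is the highest of the three event-based power figures in that section. A reader who trusts it would take a non-significant seclusion result as good evidence against a 12% benefit. If real power is far lower, that reading is wrong.

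**Working it through.** **Inputs**
- Effect: 12% reduction, read as a rate ratio of 0.88; |ln 0.88| = 0.1278 (Sample size).
- Duration: 3.60 months. With the 20% buffer this is 3.0 × 1.2 (Sample size).
- Alpha: 0.50 as printed (Sample size) and 0.05 as used for testing (Analysis plan).
- Initial result: IRR 0.37, CI 0.24 to 0.57, one unit, 15 months per period.
- Units: three intervention units (Setting).
- Assumptions: Poisson counts, equal exposure in the two initial periods, and study units similar to the initial unit.

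**Step 1: the implied event rate**
- SE(log IRR) = ln(0.57/0.24)/3.92 = 0.2207.
- Solving 1/a + 1/(0.37a) = 0.2207² gives a = (1 + 1/0.37)/0.2207² ≈ 76 events before and 0.37 × 76 ≈ 28 after.
- Rate before: 76/15 ≈ 5.07 per unit-month. Rounding of the printed limits allows 71 to 81 events before, or 4.7 to 5.4 per unit-month.

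**Step 2: try to reproduce 99.30% at 3.6 months**
- Baseline events: 3 × 3.6 × 5.07 ≈ 54.7. Under a rate ratio of 0.88: 48.2.
- SE = √(1/54.7 + 1/48.2) ≈ 0.198, and 0.1278/0.198 ≈ 0.647.
- Power = Φ(0.647 − z) + Φ(−0.647 − z), where z is the two-sided critical value.

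| Case (rate ratio 0.88, three units, two-sided) | alpha .05 | alpha 0.50 |
|---|---|---|
| 3.6 months before and after | 9.9% | 58% |
| 3.0 months (buffer removed) | 9.1% | 57% |
| 3.6 months after a 12-month baseline | 12.4% | 62% |

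A Poisson simulation of the first row gave 9.7% and 58.5%. The stated figure is not reproduced. Varying the number of units (1, 3 or 6), the length (3.0 or 3.6 months), the baseline length and the pre- or post-implementation rate gave at most 20% at two-sided .05 and 71% at two-sided 0.50. The most generous case (six units, 12-month baseline, one-sided 0.50) gave 87%.

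**Step 3: what 99.3% would need**
- Baseline events = (1 + 1/0.88) × ((z + 2.457)/0.1278)².
- Alpha .05 (z = 1.960): about 2,551 events. Divided by 10.8 unit-months this is 236 per unit-month, 47 times the implied rate, or about 24 seclusions a day across the 75 beds (2,551/108 days).
- Alpha 0.50 (z = 0.674): about 1,282 events, or 119 per unit-month, 23 times the implied rate.

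**Step 4: a higher rate, and the planned 12 months (two-sided .05, within-group)**

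| Seclusions per unit-month | 3.6 months | 12 months |
|---|---|---|
| 5.07 (implied) | 10% | 22% |
| 20 (about four times) | 25% | 65% |

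At the implied rate, 12 months give 3 × 12 × 5.07 ≈ 182.5 baseline events. A rate ratio of 0.726 then has SE = √(1/182.5 + 1/132.5) ≈ 0.114 and |ln 0.726|/0.114 ≈ 2.81, for 80% power. The detectable reduction is therefore about 27%.

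**The case against.** The strongest reply is that the baseline rate is derived, not stated. It comes from one unit, and the Setting section says the study units differ in restrictive practice rates. The sample-size text speaks of "synthetic data replicating the initial implementation outcome parameters" without pointing to the 0.37 result, and it takes effect sizes from an evaluation not shown here. The model behind the 0.24 to 0.57 interval is not given either. If that interval already allowed for overdispersion, the raw count exceeded 76, and a plain Poisson simulation on raw counts would credit more information. All of this stands, and it makes 5 per unit-month approximate. It does not plausibly supply a factor of 23 to 47.

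The trial also does not stop at 3.6 months. It compares a year with a year, so the 10% figure tests the printed claim and is not the power of the trial.

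Four stronger readings are tempting but unsupported:
- **That the claim is impossible outright.** The simulation inputs are not shown. The conflict is with the derived rate and a relative reading of 12%.
- **That the power was really computed for IRR 0.37.** On the same events that gives 96.9% at .05 and 99.9% at 0.50, neither of which is 99.30%.
- **That 12% means an absolute drop of 0.12 seclusions per unit-day.** This does give 99.3% at two-sided .05 (0.167 to 0.047 a day), but it is a 72% relative fall, and nothing in the text describes the effect that way.
- **That the baseline-year rate is already in hand.** The article says only that collection of those data began alongside recruitment.

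I give no between-group power. It would need control-unit rates the article does not report, and the planned analysis is weighted.

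**Conclusion.** The point holds in a conditional form. Read as a relative reduction, the stated effect, duration and power do not fit together at the seclusion rate implied by the article's own initial result. Power is about 10% at the level used for testing and about 58% at the printed 0.50, against 99.30% stated. Correcting the alpha alone widens the gap.

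For the planned 12 months, within-group power for a 12% reduction is about 22% at the implied rate and about 65% at 20 per unit-month. A non-significant seclusion result could not exclude a 12% benefit in either case. The exact percentages rest on the assumptions listed with the inputs. The conclusion that 99.30% at 3.6 months is not credible survives large departures from them.

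**What to change.** Rerun the simulation at alpha .05 and state the effect scale (relative or absolute), the baseline seclusion rate, the number of units able to seclude and the planned contrast. Replace the 99.30%/3.60-month sentence with the 12-month power and the minimum detectable rate ratio, separately for the within-group and between-group tests. Use the observed baseline-year rate when it is available. If the simulated effect was something other than a 12% relative reduction, state that effect.

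The cost is a rerun and a corrected paragraph. No units or follow-up are added, and with data collection due to end on 15 April 2025 the design itself would not change. The downside is a less favourable stated power.

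### The event-based power simulations are reported at alpha 0.50, but every hypothesis is to be tested at p < .05; the article does not show which level was run

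*Protocol article*

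**What the plan says.** The Sample size section of the protocol article plans the event-based outcomes by simulation: "Monte Carlo simulations using the simr package [59] and RStudio [60], were used to estimate the necessary duration of data collection". On the model it says: "A Poisson mixed-effects model was applied to synthetic data replicating the initial implementation outcome parameters". Three results follow:

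- Seclusion: "To detect a 12% reduction in seclusion rates with 99.30% power, at least 3.60 months of data collection is required".
- Physical restraint: "To identify significant changes in physical restraint incidents, a 12-month period is necessary to achieve 90.60% power".
- Code Black/Assist: "10.8 months are required to detect differences in Code Black/ Assist events with 85.20% power".

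The section then says that these calculations carry a 20% buffer and "were conducted with an alpha level of 0.50, aligning effect size assumptions with findings from the NSW Safewards evaluation". That sentence covers all three results.

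The Analysis plan sets the decision rule: "Each hypothesis will be supported if outcomes are statistically significant at p < .05". It does not say whether tests are one- or two-sided, and it gives no other threshold for the event outcomes.

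**The concern.** Power belongs to a particular significance level. A power simulated at 0.50 does not carry over to a test at .05, because the critical value rises from about 0.67 to 1.96 (two-sided) while the signal stays the same. As printed, the planning level and the testing level cannot both describe the same test.

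The consequence falls on how a null result is read. Physical restraint needs the full 12 months to reach its stated 90.60%, so it has no slack within the one-year follow-up. A reader who sees no significant change in restraint needs to know whether the study had about nine chances in ten of detecting its assumed effect or about one in two. The article does not allow that to be settled.

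**Working it through.** **Can the stated powers be reproduced?** No. They come from simulations of a Poisson mixed model. The article gives no baseline event rates, random-effect variances or number of simulations, and it prints an effect size only for seclusion (12%). What can be computed is the consequence if 0.50 was literal.

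**Inputs.** Stated powers 0.993, 0.906 and 0.852; stated durations 3.6, 12 and 10.8 months; printed alpha 0.50 (all Sample size); test level .05 (Analysis plan). Assumptions: approximately normal test statistic, two-sided at both levels, same model and effect.

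**Step 1: recover the signal.** With critical value z(0.75) = 0.674 for alpha 0.50, solve for d in

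Φ(d − 0.674) + Φ(−d − 0.674) = stated power.

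This gives d = 3.128 (seclusion), 1.967 (restraint) and 1.680 (Code Black/Assist). Check for restraint: Φ(1.293) + Φ(−2.641) = 0.902 + 0.004 = 0.906.

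**Step 2: power at .05.** Evaluate Φ(d − 1.960) + Φ(−d − 1.960). The second term is negligible.

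| Outcome | Stated power | d | d − 1.960 | Power at .05 if 0.50 was run | If 0.50 is a misprint |
|---|---|---|---|---|---|
| Seclusion, 3.6 months | 99.3% | 3.128 | 1.168 | 87.9% | 99.3% |
| Physical restraint, 12 months | 90.6% | 1.967 | 0.007 | 50.3% | 90.6% |
| Code Black/Assist, 10.8 months | 85.2% | 1.680 | −0.280 | 39.0% | 85.2% |

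Dropping the opposite tail in both steps changes these only slightly (87.9%, 51.2%, 40.5%).

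**Step 3: sensitivity to sidedness.** If 0.50 was one-sided, its critical value is 0, so d = z(power) = 2.457, 1.317 and 1.045. Power is then about 79%, 37% and 27% at one-sided .05 (critical value 1.645), or about 69%, 26% and 18% at two-sided .05.

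**Step 4: durations and 12-month power, if 0.50 was run.** Taking d to grow with the square root of time, the months needed to keep the stated power at two-sided .05 are months × ((1.960 + z(power)) / d)²:

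- Seclusion: 3.6 × (4.417 / 3.128)² ≈ 7.2 months.
- Restraint: 12 × (3.277 / 1.967)² ≈ 33 months.
- Code Black/Assist: 10.8 × (3.005 / 1.680)² ≈ 35 months.

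At 12 months, d is 3.128 × √(12/3.6) = 5.71 for seclusion (power above 99.9%) and 1.680 × √(12/10.8) = 1.77 for Code Black/Assist (power about 43%). Restraint stays at about 50%. So even on the literal reading, seclusion would be well powered over the full year; the shortfall would lie in the other two.

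**Step 5: can the document reveal which alpha was run?** For two equal Poisson periods and a rate ratio of 0.88, the baseline-period events needed for 99.3% power are E = (1 + 1/0.88) × ((z_alpha + 2.457) / |ln 0.88|)². That is about 2,551 at alpha .05 and about 1,282 at alpha 0.50, or roughly 23 and 12 seclusions a day over 3.6 months. The article gives no event rate to compare with either, so this does not decide the matter.

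**The case against.** A reader might infer from the two sections that every stated event-based power is overstated. The documents do not support that. An alpha of 0.50 is not a level anyone would normally plan with, a shifted decimal explains it, the only threshold applied to the hypotheses is .05, and the Sample size section itself speaks of identifying significant changes. A misprint is at least as plausible as a literal 0.50, and then no power changes on this account. That argument stands, and it makes every reduced figure above conditional.

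A reader might also infer that the one-year follow-up rests on these powers and would be undermined with them. That is not supported either. The Design section justifies one year by the time within which such implementation efforts are said to consolidate, and ties the quarterly time points to the phased training. The Intervention section describes a one-year programme. The Sample size section says that power analyses were combined with prior research and feasibility.

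It is also fair to say that the reduced figures carry a normal approximation over to a simulated mixed model, and that the p < .05 decision rule is unaffected, so type I error control is not in question here.

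None of this removes the contradiction. On either reading the Sample size paragraph is wrong for the test that the Analysis plan specifies. Nor is this a detail left to a fuller document: a specific value is printed, and it conflicts with another printed value.

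**Conclusion.** The inconsistency is certain; its effect on power is not. One of two things is wrong: the printed alpha, or the three powers and durations reported under it.

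The effect ranges from none (0.50 is a misprint for 0.05) to a fall to about 88%, 50% and 39% for seclusion, restraint and Code Black/Assist at their stated durations (0.50 was run, two-sided at both levels). One-sided readings of 0.50 would give lower figures. The reduced figures assume a normal approximation with the same effect and model, and are not a rerun of the simulations. The point needs correction in either case because the alpha governs all the event-based power statements and only the study team can say which level was used.

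**What to change.** Check the alpha in the simr script.

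- If it was .05, change the stated alpha in the Sample size section to 0.05. The powers and durations stay as they are on this point.
- If it was 0.50, rerun the simulations at two-sided .05. Replace the three powers and durations, and state the power that the 12-month follow-up delivers for each outcome.

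In either case, state in the Sample size section whether the level is one- or two-sided, so that it can be matched to the Analysis plan.

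The cost is one look at an existing script, then either a one-figure correction or a rerun and an edited paragraph. If a rerun is needed, the restated powers for restraint and Code Black/Assist may be much less favourable. No design change or longer follow-up is required.
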